#### Psychoeducation on depression condition **
*(*
**OPD**
*)*
**

The OPD intervention is also Internet-based and is implemented on the same platform as GET.ON Mood Enhancer. In the current study, the psychoeducational intervention is based on the patient version of the German S3-Guideline/National Disease Management Guideline Unipolar Depression [34]. It informs participants about the nature and evidence-based treatments of depression including information about symptoms, strategies to overcome depression and sources of help. In this study, the psychoeducational intervention requires no explicit homework assignments from the participants and provides no therapist support. Passive psychoeducational interventions have been shown to be effective in reducing depressive symptoms with a pooled standardised effect size of d = 0.26 [35].

### Treatment as usual

There will be no restriction on the use of treatment as usual in routine mental health services during the study period, such as psychotherapeutic and psychiatric treatment or antidepressant medication. However, to control for potential confounding effects, treatment utilisation and changes in the dosage of antidepressant medication intake will be monitored during the study period.

### Primary and secondary outcomes

The primary outcome will be observer-rated depression severity. In the secondary analyses, we will explore the effects of the treatments on self-reported depression severity, wellbeing, anxiety symptoms, quality of life and the number of patients who (1) responded and (2) are in remission. Moreover, we will also systematically evaluate potential negative treatment effects (that is, symptom deteriorations, negative effects on attitudes towards seeking psychological help; other adverse events).

### Measures

#### Primary outcome

The primary outcome will be observer-based rating of depressive symptom severity measured by the Hamilton Rating Scale for Depression HRSD_24_[36-38]. The HRSD is likely to be the most widely used clinician-rated scale for measuring depression in research. The self-report measure assesses depressed mood, vegetative and cognitive symptoms of depression, and anxiety symptoms. Items are rated on either a 5-point or a 3-point scale, and the total score is derived by summing the individual item scores. Higher scores indicate greater symptom severity. The HRSD is sensitive to change, inter-rater reliability is 0.90 [36], and the scale corresponds well with overall clinical ratings of severity [39,40]. The cutoff points of 10, 19, 27 and 35 represent the threshold for mild, moderate, severe and very severe depression, respectively.

#### Secondary outcomes

##### Depressive symptoms

As the secondary outcome, observer-based rating of depression will also be measured using the Quick Inventory of Depressive Symptomatology - Clinician-Rating QIDS-CR_16_[41,42]. The 16-item QIDS-CR_16_ is a brief clinician-report rating scale developed from the 30-item Inventory of Depressive Symptomatology [41-43]. In contrast to the HRSD, it evaluates only the nine depression criterion symptom domains (that is, sad mood, concentration, self-criticism, suicidal ideation, interest/involvement, energy/fatigability, sleep disturbance, appetite/weight change and psychomotor agitation/retardation) from the Diagnostic and Statistical Manual of Mental Disorders [44] during the prior 7 days. Each item is scored on a scale from 0 to 3 points, with higher scores indicating higher symptom severity. This measure has shown good psychometric properties, such as strong internal consistency (α = 0.85), concurrent validity and sensitivity to symptom change in patients with MDD [42]. The cutoff points of 6, 11, 16 and 21 represent the threshold for mild, moderate, severe and very severe depression, respectively.

Self-reported depressive symptoms will be assessed with the Patient Health Questionnaire (PHQ-9). This measure has comparable sensitivity and specificity to many other depression measures, although it is only half the length. Its internal reliability reaches values between α = 0.86 and 0.89 [45,46]. Each item assesses the frequency of a symptom in the last 2 weeks on a scale ranging from 0 (‘not at all’) to 3 (‘nearly every day’). In contrast to the primary outcome measure HRSD_24_, the PHQ-9 only assesses frequency of symptoms, not their intensity. The total score ranges from 0 to 27, with a higher score indicating more frequent symptoms. The cutoff points of 5, 10, 15 and 20 represent the threshold for mild, moderate, moderately severe and severe depression, respectively [45,46].

##### Quality of life

Health-related quality of life will be assessed with the SF-12v1 Health Survey [47]. The SF-12v1 has 12 items covering eight health domains (physical functioning, physical and emotional role functioning, body pain, general health, vitality, social functioning and mental health). The SF-12 generates a physical and a mental health summary score.

##### Anxiety

Anxiety will be measured with the anxiety subscale of the Hospital Anxiety and Depression Scale HADS-A [48]. The anxiety subscale consists of seven questions and each is scored from 0 to 3 with total scores ranging from 0 to 21. A score between 0 and 7 indicates no anxiety, between 8 and 10 possible anxiety, and above 11 or 12 a clinical anxiety disorder. Psychometric properties are well established [49].

##### Problem-solving skills

Problem-solving ability (that is, generalised appraisal, beliefs, expectancies and emotional responses) will be measured with two subscales of the Social Problem-Solving Inventory-Revised (SPSI-R). The positive problem orientation (PPO) subscale represents a constructive dimension, and the negative problem orientation (NPO) subscale is viewed as a dysfunctional dimension. Cronbach’s alphas are α = 0.76 for the PPO dimension and 0.83 for the NPO dimension [50].

##### Behavioural activation

Participants’ activation towards goals or values and pleasant activities and avoidance behaviours will be measured with the BADS-Short Form BADS-SF [51]. The BADS-SF entails nine items comprising two subscales (activation and avoidance). The items are rated on a 7-point Likert-type scale. Higher scores indicate that the participant scores high on the area of interest. The internal consistency is α = 0.82 [51].

##### Wellbeing

Psychological wellbeing will be measured by the World Health Organization’s (WHO) 5 Wellbeing Index [52]. Participants indicate for each of the five statements, which one is closest to how they have been feeling over the prior 2 weeks. Each question is scored from 0 to 5 with the total score ranging from 0 to 25. Higher scores indicate better wellbeing.

##### Problematic alcohol use

The Alcohol Use Disorders Identification Test (AUDIT) is a 10-item questionnaire designed by the WHO to screen for hazardous alcohol intake. It assess three conceptual domains: alcohol intake (items 1 to 3), dependence (items 4 to 6) and adverse consequences (items 7 to 10). Sum-scores can range from 0 to 40, and the generally accepted cutoff point for identifying a potential alcohol problem is 8 [53].

##### Treatment credibility/patient expectancy

Training credibility and participants’ expectancy for improvement will be measured with the credibility and expectation questionnaire (CEQ). The CEQ consists of six items which are rated on a 9- or sometimes 10-point Likert scale. The psychometric properties of the instrument are well established [54].

##### Course evaluation

In absence of a standardised measure for evaluating course satisfaction in Internet-based treatments, user satisfaction will be measured with a self-designed questionnaire based on the Client Satisfaction Questionnaire CSQ-8, German Version [55,56]. This self-report measure consists of eight items measuring the global client satisfaction with the Internet-based training. Previous research indicated a high internal consistency [57].

##### Response and remission

Participants will be coded as responders when they demonstrate a reliable change according to the widely used reliable change index (RCI) [58]. Participants with an RCI of 1.96 or above on the primary outcome measure HRSD_24_ will be considered responders. Remission is defined a priori as a non-pathological score of ≤10 on the HRSD_24_.

##### Negative effects

Negative effects will be measured on (1) symptom deterioration during treatment (2), attitudes towards seeking psychological help, and (3) other adverse events.

(1) *Symptom deteriorations*

Patients will be classified as deteriorated when they display a reliable negative change (−1.96) in the primary outcome measure HRSD_24_ according to the reliable change index, proposed by Jacobsen & Truax (1991) [58].

(2) *Negative effects on attitudes towards seeking professional psychological help*

A potential negative influence on attitudes towards seeking mental healthcare service utilisation will be measured with the Attitudes Toward Seeking Professional Psychological Help Scale-SF ATSPPH-SF [59]. The ATSPPH-SF consists of 10 items that are rated on a 4-point Likert scale from 0 to 3, yielding a total score ranging from 0 to 30. High scores indicate more positive treatment attitudes. The instrument showed good psychometric properties [60].

##### Other adverse events

Other adverse events will be measured with the negative effects of psychotherapy inventory (INEP). The INEP is a relatively new measure and was developed for assessing systematic and potentially negative effects of psychotherapeutic interventions in different domains. The version used in this study consists of 15 items assessing any negative effects participants experienced within or after the completion of the Internet-based training on (1) negative intrapersonal changes (for example, ‘During treatment or since the end of my therapy, I suffered from suicidal thoughts or intentions for the first time ever’), (2) negative effects in an intimate relationship (for example, ‘My partner is or has been jealous of my therapist’), (3) family/friends (for example, ‘The relationships with my friends has worsened’), (4) perceived dependence on the psychotherapist/psychotherapeutic intervention (for example, ‘I feel dependent on my therapist’), and (5) stigmatisation (for example, ‘I am anxious that my colleagues or friends could find out about my psychotherapy’). The items are rated on a 4-point Likert scale (0 = no agreement at all; 3 = total agreement). Chronbach’s alpha is α = 0.85 (Table 2).

**Table 2 T2:** Overview of measurements

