### Participants and procedure

#### Inclusion and exclusion criteria

We will include adults (1) above the age of 18 years (2) with MDD according to DSM-5 criteria (3) who have Internet access, (4) have sufficient German skills in reading and writing (self-report), and (5) are willing to give informed consent. We will exclude subjects (1) with a history of manic/hypomanic episodes, (2) with a history of psychotic disorders, (3) currently receiving psychotherapy for any kind of mental health problems, (4) showing a notable suicidal risk as indicated by a score greater than 1 on BDI Item 9 (‘I feel I would be better off dead’), or (5) a change in antidepressive medication dosage/drug within 4 weeks before baseline.

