#### Assessment of eligibility and randomisation

People who apply for study participation will receive an information letter with detailed information about the study procedures. Full written informed consent will be obtained from all participants. They will be informed that they can withdraw from the intervention and/or study at any time without any negative consequences. Nevertheless, we will ask those who withdraw from the trial treatment to attend all the remaining research appointments or at least provide minimal data (primary outcome measure). Applicants who continue to participate in the study will be asked to complete online screening questionnaires to assess the severity of their depressive symptoms (CES-D >16), whether they are currently receiving any kind of treatment for any mental health disease and whether they have a high suicidal risk (BDI Item 9 > 1). Subjects screened positive and are willing to give informed consent will be scheduled for a structured clinical interview (SCID) conducted via the telephone [27]. SCIDs will be conducted by trained clinicians. Participants meeting all of the inclusion and none of the exclusion criteria, who have completed the baseline assessment, and returned the informed consent form will enter the study and will be randomly allocated to study conditions. Randomisation will take place at an individual level. The allocation will be performed by an independent researcher not otherwise involved in the study using an automated computer-based random integer generator (randlist). The allocation will be concealed in advance from participants, researchers involved in recruitment, and therapists.

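### The negative-effects definitions include no measure specific to worsening or recurrent suicidal ideation, although a suitable clinician-rated item is already collected

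*Protocol article*

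**What the plan says.** **Entry.** The section on inclusion and exclusion criteria excludes people "showing a notable suicidal risk as indicated by a score greater than 1 on BDI Item 9". The eligibility section applies the same threshold at online screening, asking "whether they have a high suicidal risk (BDI Item 9 > 1". Scores of 0 and 1 are therefore eligible. Past suicidal thoughts are not among the exclusion criteria.

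**Definition of harm.** The Negative effects section gives a list of three: "Negative effects will be measured on (1) symptom deterioration during treatment (2), attitudes towards seeking psychological help, and (3) other adverse events". For the first, "Patients will be classified as deteriorated when they display a reliable negative change (−1.96) in the primary outcome measure HRSD_24", using the reliable change index. The second is the ATSPPH-SF attitude scale. The third is the INEP, described in these terms: "The version used in this study consists of 15 items assessing any negative effects participants experienced within or after the completion of the Internet-based training". One example is quoted for each of five INEP domains. The example for negative intrapersonal changes reads "I suffered from suicidal thoughts or intentions for the first time ever". Items are rated on a 4-point agreement scale.

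**Other data on ideation.** The secondary outcome QIDS-CR16 is clinician-rated. Its listed domains begin "sad mood, concentration, self-criticism, suicidal ideation, interest/involvement", and each item is scored 0 to 3. Table 2 schedules the QIDS at T1, T2 and T3, and the INEP at T2 and T3 only.

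**The concern.** Worsening suicidality is an obvious harm to look for in a trial of a low-intensity intervention for major depression, and the article presents its evaluation of negative effects as a main strength. The one suicidality item it names records first-ever onset. A participant who has had such thoughts before, and whose thoughts return or intensify during the trial, does not fit that wording. The INEP has no baseline, so change since entry cannot be computed from it either.

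What is at stake is how a reassuring result would be read. If few participants endorse the item, that may partly reflect its wording rather than an absence of worsening among people with prior ideation. The closing paragraph of the Discussion links wider dissemination to an acceptable balance of risk and benefit, so readers are likely to lean on the negative-effects results.

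**Working it through.** The plan gives no figure on this point to reproduce. The check is mainly a comparison of definitions, with one calculation on the HRSD-24 criterion.

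**Step 1: who can enter.** A BDI item 9 score of 1 is eligible. The article gives only the item's label and does not say what a score of 1 means, so reading it as current mild ideation is an assumption. The point does not need that assumption, because past ideation is not an exclusion.

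**Step 2: what the named INEP item can register.** It asks about thoughts or intentions occurring for the first time. A participant with any earlier ideation cannot truthfully agree with it, whatever happens after randomisation.

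**Step 3: whether HRSD-24 deterioration closes the gap.** The criterion applies to the total score. The reliable change threshold is 1.96 × SD × √(2 × (1 − r)). The only HRSD reliability in the article is an inter-rater value of 0.90. Using it as r is an assumption, as is a baseline SD of 6 to 9 points. The values of r on either side of 0.90 are also assumed, to show the range.

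| r | Threshold in SD units | SD = 6 | SD = 9 | Largest SD at which 4 points suffice |
|---|---|---|---|---|
| 0.95 | 1.96 × √0.10 = 0.620 | 3.7 points | 5.6 points | 4 / 0.620 = 6.5 |
| 0.90 | 1.96 × √0.20 = 0.877 | 5.3 points | 7.9 points | 4 / 0.877 = 4.6 |
| 0.80 | 1.96 × √0.40 = 1.240 | 7.4 points | 11.2 points | 4 / 1.240 = 3.2 |

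HRSD items have at most five response levels, so one item can move the total by at most 4 points. With the article's 0.90, worsening confined to one item misses the threshold across the whole assumed SD range. It can reach the threshold only in the most favourable corner (r = 0.95, SD near 6), and then only by moving from the bottom to the top of a 5-point item. Improvement on other items would offset it further. Ideation that worsens together with depression generally can cross the threshold and would be counted.

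**Step 4: whether another planned measure could do the job.** The QIDS-CR16 ideation item is clinician-rated at baseline and at both later assessments, so change from T1 is computable for everyone assessed. The article uses the QIDS only as a secondary measure of depression severity. No rule turns a rise in this item into a negative effect.

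**The case against.** The strongest case against has four parts.

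- **The INEP is mostly unseen.** The first-onset item is offered as an example from a 15-item inventory. Another item may cover worsening or returning ideation. This stands. A reader might infer that such worsening is bound to go unrecorded, but the documents do not support that.
- **No forced answer.** A reader might also infer that a participant with prior ideation has to answer no. The scale has four levels of agreement, so the most that can be said is that such a person cannot truthfully agree. This stands too.
- **Other routes exist, and the ratio is unaffected.** Broad worsening can be counted as HRSD-24 deterioration, and the QIDS data will exist. The formal benefit-risk ratio divides the number needed to harm for symptom deterioration by the number needed to treat for response. The INEP item does not enter it and cannot distort it. All of this is correct. It narrows the gap but leaves worsening of ideation alone without a definition.
- **Item-level tabulation is detail for a fuller document.** This carries weight, and nothing in the article is contradictory here. However, the article itself fixes the three components of harm, the deterioration criterion and the tests. The gap lies in definitions it chose to state.

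A head count of affected participants is also tempting. The documents give no prevalence of prior ideation, and such a count would describe people who cannot endorse one item, not events missed.

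**Conclusion.** The point holds as a cheap improvement, not as an error in the plan. The stated negative-effects definitions contain nothing specific to worsening of existing or recurrent suicidal ideation. The one suicidality item named concerns first-ever thoughts and has no baseline. The HRSD-24 total need not respond to worsening of ideation alone.

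The size cannot be given as a number of participants or events. In practical terms it is one missing definition and one missing table, for data that are already scheduled. The conclusion rests on the items the article shows. If an INEP item that is not shown covers recurrence or worsening, the gap is smaller. The HRSD-24 calculation also depends on the assumed SD and on using the inter-rater reliability in the index.

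**What to change.** In the Negative effects section, add an exploratory negative effect: an increase from T1 on the clinician-rated QIDS-CR16 suicidal ideation item, assessed at T2 and at T3. Tabulate it by arm, with the number assessed at each time, and compare the arms with the methods the Statistical analyses section already plans for categorical and binary negative effects. Report the INEP item separately and label it as first-ever onset only.

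This takes about two sentences of text and one more table, with no new instrument or visit. The downside is one more exploratory comparison with few events, so the counts should be presented descriptively and the absence of a significant difference should not be read as evidence of safety. A participant already at the top score of 3 at T1 cannot show an increase, so the baseline distribution should be shown alongside. The change concerns outcome reporting only. It alters neither the entry rule nor any aspect of clinical management.

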		**Time of measurement**		
**Instrument**	**Aim**	**T1 ****(****Baseline****)**	**T2 ****(****6 weeks****)**	**T3 ****(****12 weeks****)**
**SCID**	Diagnostic interview	x		
**HRSD**_ **24** _	Hamilton Rating Scale for Depression	x	x	x
**QIDS**-**C**_ **16** _	Quick Inventory for Depressive Symptomatology	x	x	x
**PHQ**-**9**	Depressive symptomatology	x	x	x
**WHO**-**5**	Wellbeing	x	x	x
**SF**-**12**	Quality of life	x	x	x
**HADS**-**A**	Anxiety symptoms	x	x	x
**SPSI**-**R**	Problem-solving skills	x	x	x
**BADS**-**SF**	Behavioural activation	x	x	x
**CEQ**	Patient expectancy/treatment credibility	x		
**ATSPPH**-**SF**	Attitudes toward seeking psychological help	x	x	
**BFI**	Big Five Inventory	x		
**INEP**	Inventory of negative effects in psychotherapy		x	x
**CSQ**-**8**	Clients’ satisfaction with the online training		x	
**AUDIT**	Alcohol use disorder identification test	x		
**Other questions**	Socio-demographics	x		

### Sample size calculation

We aim to include 128 participants. This sample will allow us to detect a between-group effect size (ES) of d = 0.50 with a power (1-ß) of 80% and an alpha of 0.05 (calculated using PASS 12). The most recent meta-analytic review found a mean ES of d = 0.78 for therapist-supported web-based interventions for depression [19]. However, most of the included studies used a waiting-list control comparison only, and these studies showed a considerably larger ES than those studies including a treatment-as-usual condition. Our comparison condition will include psychoeducation and full access to treatment as usual and participants are encouraged to seek further help. Thus, we expect a somewhat smaller ES of d = 0.50 at post-treatment.

### Statistical analyses

The clinical trial will be conducted in compliance with the Declaration of Helsinki, the CONSORT guidelines, GCP and the protocol. Aiming at an intention-to-treat design [61] we will include all participants who will be randomly assigned to one of the two conditions. Additional per protocol analyses (PPA) will be conducted, including only participants’ satisfying protocol treatment (completed at least 4 of 6 modules). Mixed-model analyses of variance will be conducted to explore the effects of the treatments on all continuous outcomes. Missing data will be handled using multiple imputations (MI). MI is especially robust with respect to missing data [62]. Nevertheless, to assess systematic effects of non-ignorable missing data, pattern mixture analyses for multi-level longitudinal approaches [63] will be conducted. To determine if the treatment effect is dependent on missing data, the missing-data pattern of each participant will be first coded and then included in a three-way interaction (missing pattern × condition × change in depression severity) in the main outcome analyses. If no significant interactions between missing-data pattern and treatment outcome are found, we will conclude that no missing data bias occurred in the results. For all mixed-model analyses, Cohen’s d [64] will be calculated by standardising the differences between baseline and follow-up scores by the pooled standard deviation of the baseline scores. Response and remission rates will be compared across groups with the help of contingency tables and χ2 tests. We will also calculate the number needed-to-be-treated (NNT) with GET.ON Mood Enhancer to achieve one response and remission, respectively, compared to the control group. We will also calculate the number needed-to-harm, which indicates the number of participants treated in the experimental condition for one extra person to have a symptom deterioration. Because the differential risk of the intervention ideally needs to be set into relation with its benefits we will also calculate a benefit-risk ratio [65]. Benefit-risk ratio will be calculated by dividing the NNH to achieve one symptom deterioration through the NNT to achieve one response. If this benefit-risk ratio is greater than 1, the benefits outweigh the risks; if it is 1, the balance between benefit and risks are equal across the groups; if it is less than 1, the risks outweigh the benefits (LIT). Benefit-risk ratios will only be calculated when differences in risk for symptom deteriorations are statistically significant.

For other negative effects, we will use independent t-tests for continuous, χ^
*2*
^ for categorical, and logistic regression for binary outcomes. In a pre-planned subgroup analysis, we will explore negative effects of GET.ON Mood Enhancer on attitudes towards seeking psychological help in patients who do not reach the response criteria up to post-assessment (6 weeks). For all statistical analyses, significance level will be set at *P* <0.05. All analyses will be conducted using SPSS 20.

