**Methods/design:**

A RCT will be conducted to compare the efficacy of GET.ON Mood Enhancer with an active control condition receiving online psychoeducation on depression (OPD). Both treatment groups will have full access to treatment as usual. Adults with MDD (*n* = 128) will be recruited and randomised to one of the two conditions. Primary outcome will be observer-rated depressive symptoms (HRSD-24) by independent assessors blind to treatment conditions. Secondary outcomes include changes in self-reported depressive symptom severity, anxiety and quality of life. Additionally, potential negative effects of the treatments will systematically be evaluated on several dimensions (for example, symptom deteriorations, attitudes toward seeking psychological help, relationships and stigmatisation). Assessments will take place at baseline, 6 and 12 weeks after randomisation.

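### The sample size assumes a two-group comparison at post-treatment, but the analysis section implies a condition × time test with no named primary time point; a baseline-adjusted T2 contrast would align them and keep at least 80% power

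*Protocol article*

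**What the plan says.** The Sample size calculation section states "We aim to include 128 participants" and says this number suffices to "detect a between-group effect size (ES) of d = 0.50 with a power (1-ß) of 80% and an alpha of 0.05". It ties the effect to one time point: "Thus, we expect a somewhat smaller ES of d = 0.50 at post-treatment". It mentions no repeated-measures model, pre-post correlation or baseline adjustment.

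The Statistical analyses section says "Mixed-model analyses of variance will be conducted to explore the effects of the treatments on all continuous outcomes". It does not list the model terms or say whether baseline is an outcome occasion or a covariate. Two later statements in that section bear on this:

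- The missing-data check enters the missingness pattern into a "three-way interaction (missing pattern × condition × change in depression severity) in the main outcome analyses".
- Cohen's d for the mixed models is obtained by "standardising the differences between baseline and follow-up scores by the pooled standard deviation of the baseline scores".

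The Objective and research questions section frames the primary hypothesis as a larger reduction in observer-rated symptoms under the intervention. Table 2 schedules the HRSD-24 at T1, T2 and T3. The sections that define the primary outcome name the scale but no time point.

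**The concern.** Three quantities serve one primary question: a between-group difference at T2 for the sample size, a condition × change effect for the test, and a baseline-standardised change for the reported effect size. They need not agree.

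At stake is whether the stated 80% power applies to the test that will be run, and whether the reported d can be set beside the planned 0.50. A difference in change carries the sampling error of both baseline and T2. When the two are only weakly correlated, it is less precise than a plain comparison at T2. Adjusting for baseline as a covariate is at least as precise as either at any correlation. The baseline HRSD-24 is already scheduled, so that precision is available at no cost.

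**Working it through.** **Inputs.** N = 128, d = 0.50, power 80% and alpha 0.05 come from the Sample size calculation section. Allocation ratio is not stated (participants are "recruited and randomised to one of the two conditions"); 1:1 is assumed. Sidedness is not stated ("For all statistical analyses, significance level will be set at" P < 0.05); two-sided is assumed. Rho, the baseline–T2 correlation of the HRSD-24, is not given; 0.3 to 0.6 is assumed as a range. Data are taken as complete. The T2 SD is set to 1.

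**Step 1: the plan's own figure.** In a two-sample t-test with 64 per arm, the noncentrality is 0.50 × √(64/2) = 2.83 on 126 df, which gives power 0.801. With 63 per arm it is 0.795. So 64 per arm, 128 in total, is the smallest size that reaches 80%. A one-sided test would need only about 50 per arm, so 128 fits the two-sided reading. The stated N is right for a comparison at a single time point.

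**Step 2: T1–T2 change contrast (condition × time over two occasions).** With equal SDs, the SD of change is √(2(1 − rho)), so the effect becomes 0.50/√(2(1 − rho)).

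**Step 3: baseline-adjusted T2 contrast.** The residual SD is √(1 − rho²), so the effect becomes 0.50/√(1 − rho²).

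| rho | Change: effect | Change: power | Adjusted T2: effect | Adjusted T2: power |
|---|---|---|---|---|
| 0.3 | 0.423 | 0.66 | 0.524 | 0.84 |
| 0.4 | 0.456 | 0.73 | 0.546 | 0.86 |
| 0.5 | 0.500 | 0.80 | 0.577 | 0.90 |
| 0.6 | 0.559 | 0.88 | 0.625 | 0.94 |

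The change contrast breaks even with the stated power where 2(1 − rho) = 1, that is, at rho = 0.50. The adjusted contrast is never worse than the change contrast, because 2(1 − rho) − (1 − rho²) = (1 − rho)², which cannot be negative. It never falls below the stated power, because 1 − rho² cannot exceed 1.

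**Step 4: unequal SDs.** If the baseline SD is k times the T2 SD, the SD of change is √(1 + k² − 2k·rho), and break-even moves to rho = k/2. For k from 0.7 to 0.9 that is 0.35 to 0.45. At k = 0.7 the change contrast has power 0.77 at rho 0.3 and 0.83 at rho 0.4; at k = 0.9 it has 0.70 and 0.77. The adjusted contrast does not depend on k.

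**Step 5: 2-df interaction over T1, T2 and T3** (equal SDs and one common correlation). If the effect stays at 0.50 at T3, power is 0.68, 0.76, 0.83 and 0.91 at rho 0.3 to 0.6, with break-even at about 0.46. If it halves at T3, power is 0.55, 0.62, 0.71 and 0.81, with break-even at about 0.59.

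**The case against.** The strongest reply is that the article never writes condition × time and never says that baseline is an outcome. Model terms are commonly left to the analysis plan, and a mixed model with baseline as a covariate, or with baseline means constrained equal, would lose no power. This stands in part. The reading is an inference, but the condition × change term, the d formula and the hypothesis of a greater reduction all point to it, and nothing in the article points to baseline as a covariate.

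It can also be said that the sample-size section already ties the effect to post-treatment, and that the Design section labels T2 post-treatment and T3 follow-up. That shows the intention, but neither the outcome sections nor the analysis section makes T2 the primary contrast.

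Four stronger readings are tempting and are not supported:

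- **The trial is underpowered.** No correlation is given. Above about 0.5, a moderate value, the implied T1–T2 test has more power than stated.
- **The reported d is a within-arm quantity.** The wording also permits a difference in change between arms over the pooled baseline SD.
- **The type I error is inflated by testing T2 and T3 separately.** Nothing says that both are tested for the primary claim, and a 2-df interaction is one test.
- **The entry criteria narrow the baseline SD.** Entry rests on an MDD diagnosis and a CES-D screen. There is no HRSD-24 threshold and no SD is given. The 0.7 to 0.9 ratio used in the working is only a sensitivity range.

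**Conclusion.** The point holds as a mismatch between the sample-size and analysis sections, not as a proven loss of power. The stated N reproduces exactly for a two-group comparison at T2, whereas the analysis text most naturally describes a change-based test over three occasions with no named primary time point. Under that reading, 80% power is reached only if the pre-post correlation is about 0.5 or more for the T1–T2 contrast. The threshold is about 0.35 to 0.45 if the baseline SD is 0.7 to 0.9 of the T2 SD, and about 0.46 to 0.59 for the 2-df interaction, depending on whether the effect persists or halves at T3. These figures assume 1:1 allocation, two-sided alpha 0.05 and complete data; apart from the 0.35 to 0.45 range they also assume equal SDs.

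A baseline-adjusted T2 contrast removes the dependence: power is 0.84 to 0.94 over rho 0.3 to 0.6 and at least 0.80 at any rho. It is a better choice than the implied test whatever the correlation proves to be. The d, as worded, also leaves unclear whether it is on the scale of the planned 0.50.

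**What to change.** - Name the baseline-adjusted between-group difference in HRSD-24 at T2 (6 weeks) as the single primary contrast.
- Estimate it from a mixed model on T2 and T3 with baseline HRSD-24 as a covariate (with its interaction with time), or from a model on all three occasions with baseline means constrained equal across arms.
- Make T3 secondary.
- Report a between-group d for the primary contrast with its confidence interval, and state which SD standardises it, so that it can be compared with the planned 0.50. A pre-post d may stay as a descriptive figure.

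The cost is a few sentences. Table 2 already schedules the HRSD-24 at all three occasions, so no further participants or measurements are needed. T3 gives up any claim to be co-primary. Recruitment was still under way when the article was submitted, so the change could be recorded before the outcome analysis.
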